### 2.2. Secondary Objectives

○Number of UTIs under non-antibiotic prophylaxis necessitating antibiotic treatment;○Evaluation of antibiotic resistance of inherent microbial flora and acquired urine cultures;○Evaluation of antibiotic consumption (DDD-defined daily doses) under non-antibiotic prophylaxis;○Evaluation of quality of life in patients undergoing non-antibiotic prophylaxis.

## 3. Design

This is a prospective, longitudinal, multi-arm, multi-centre, observational, clinical cohort study. Patients will receive approved non-antibiotic UTI prophylaxis with either *Escherichia coli* viva OM-89 (UroVaxom^®^), bacterial lysate vaccine (StroVac^®^), nasturtium and horseradish root powder (Angocin^®^), D-Mannose or bladder irrigation with saline once daily. Occurring complications under named prophylaxis will be treated according to the current standard of care. 

Primary Outcome Measure: Incidence of symptomatic breakthrough infections.

Secondary Outcomes: Severity of infectious breakouts with antibiotic use, development of antibiotic-resistant (AMR) flora, number of antibiotics used, quality of life, and exploration of health economic assessment variables. 

## 4. Participants

Adult patients with neurogenic bladder dysfunction, practising clean intermittent self-catheterization, who suffer from recurrent UTI (used definition: more than 3 episodes in the last 12 months) and who failed conservative measures. Non-antibiotic prophylaxis (UroVaxom, StroVac, Angocin, D-mannose, saline bladder irrigation) will be offered to these patients per-protocol basis. The data of the bacterial isolates and their susceptibility results used in this study will be obtained as part of routine clinical care. The necessity of informed patient consent is at the discretion of the participating institution. All patient data will be analysed anonymously.

### 4.1. Inclusion Criteria

Microbiologically proven UTI according to Section 1.3;Age > 18;Ability to consent;NLUTD with practised ISC;rUTI (used definition: more than 3 infections per year) independent from a bacterial spectrum of infection;Failed conservative measures (e.g., an increase in fluid intake and an increase in assisted bladder emptying);Previous episodes of UTIs do not show multi-drug-resistant bacteria;Non-antibiotic prophylaxis with UroVaxom, StroVac, Angocin, D-Mannose or bladder irrigation with saline;Signed informed consent form.

### 4.2. Exclusion Criteria

Patients practising ISC with augmented bladder or continent pouches;Inability to consent;Intention-to-treat analysis for dropouts;Failure to provide consent;MDR pathogens in previous episodes of UTIs;Antibiotic prophylaxis in the months before study enrolment.

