## Abstract

Introduction: Patients with neurogenic lower urinary tract dysfunction (NLUTD) reliant on intermittent self-catheterization for bladder emptying are at an increased risk of recurrent urinary tract infections (rUTI). So far, the most common practice in the prevention of rUTIs is long-term low-dose antibiotic prophylaxis, phytotherapy, and immunomodulation, whereby antibiotic prophylaxis inevitably leads to the emergence of drug-resistant pathogens and difficulty in treating infections. Therefore, non-antibiotic alternatives in the prevention of rUTIs are urgently required. We aim to identify the comparative clinical effectiveness of a non-antibiotic prophylaxis regimen in the prevention of recurrent urinary tract infections in patients with neurogenic bladder dysfunction who practice intermittent self-catheterization. Methods and analysis: In this multi-centre, prospective longitudinal multi-arm observational study, a total of 785 patients practising intermittent self-catheterisation due to NLUTD will be included. After inclusion, non-antibiotic prophylaxis regimens will be instilled with either UroVaxom^®^ (OM-89) standard regimen, StroVac^®^ (bacterial lysate vaccine) standard regimen, Angocin^®^, D-mannose (oral dose 2 g), bladder irrigation with saline (once per day). The management protocols will be pre-defined, but the selection of the protocol will be at the clinicians’ discretion. Patients will be followed for 12 months from the onset of the prophylaxis protocol. The primary outcome is to identify the incidence of breakthrough infections. The secondary outcomes are adverse events associated with the prophylaxis regimens and the severity of breakthrough infections. Other outcomes include the exploration of change in susceptibility pattern via the optional rectal and perineal swab, as well as health-related quality of life over time (HRQoL), which will be measured in a random subgroup of 30 patients. Ethics and dissemination: Ethical approval for this study has been granted by the ethical review board of the University Medical Centre Rostock (A 2021-0238 from 28 October 2021). The results will be published in a peer-reviewed journal and presented at relevant meetings. Study registration number: German Clinical Trials Register: Number DRKS00029142.

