## 5. Patients Recruitment

Identification of observations: Patients to be observed will be identified through participating clinicians in either an outpatient setting, hospitalised patients or follow-up visits after symptomatic infections. The eligibility criteria checklist of all cases considered to be observed will be filled in by participating principal investigators (PI). Clinical information from the initial diagnosis should be used to assess eligibility.

A logbook of patient screening will be kept to keep track of the number of patients per unit who are eligible and who are not. We will also keep track of those who are eligible and refuse to participate. If recruitment rates are slower than the anticipated trajectory, the logbook will be reviewed to identify obstacles in recruitment. 

Patients will be stratified to balance our groups according to age, sex, underlying neurological condition and number of infections prior to study inclusion. 

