## 6. Observations

### 6.1. Demographic Characterization—Baseline

Age;Country;Sex;BMI;Underlying neurological disease;Date of initial diagnosis;Charlson Comorbidity Index;Medication;ACSS score;Practice of sterile intermittent self-catheterization;Practice of clean intermittent self-catheterization;Duration of practised catheterisation in months;Number of catheterisations per day;Number of UTIs in last 12 months;Hospitalisation due to UTI;Earlier prophylaxis regimens/sufficiency of prophylaxis (prophylaxis regimen with duration and dosing, Patient impression, reduction of UTI in three months);Appropriateness of intermittent self-catheterization (measured by post-void residual (PVR) via ultrasound, which should be less than 100–150 mls).

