### 6.2. Non-Antibiotic Prophylaxis Regimen

UroVaxom (OM-89) will be administered as a standard regimen: once daily for three months with a three-month pause following and three ten-day cycles at 7, 8 and 9 months.,StroVac (bacterial lysate vaccine) standard regimen: three vaccines in 6–12 weeks with two weeks between each vaccination *.Angocin twice daily for the duration of the study.D-mannose (oral dose 2 g) once daily for the duration of the studyBladder irrigation with saline (0.9%; 250 mL) once per day for the duration of the study.

* In case of restricted drug availability due to country-specific authorisation of vaccines, additional treatment arms with similar mechanisms of action will be opened and analysed as a subgroup. If necessary, amendments to the protocol will be issued, and additional ethics approval will be requested.

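### Entry rules screen for earlier antibiotic prophylaxis only, over an unnumbered period, so residual effect of a recently finished OM-89 or StroVac course can be counted under another study regimen

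*Protocol article*

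**What the plan says.** Protocol article, Section 4.2 excludes "Antibiotic prophylaxis in the months before study enrolment". It gives no number of months, and no other exclusion concerns earlier prophylaxis. Section 4.1 lists as an inclusion item "Non-antibiotic prophylaxis with UroVaxom, StroVac, Angocin, D-Mannose or bladder irrigation with saline", with no condition that the regimen be newly started or that the patient has not recently used another of the five.

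Previously treated patients are expected. The baseline list in Section 6.1 records "Earlier prophylaxis regimens/sufficiency of prophylaxis (prophylaxis regimen with duration and dosing, Patient impression, reduction of UTI in three months" and so on, but asks for no stop date.

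On timing, the Abstract says "After inclusion, non-antibiotic prophylaxis regimens will be instilled" and "Patients will be followed for 12 months from the onset of the prophylaxis protocol". Section 6.2 gives OM-89 "once daily for three months with a three-month pause following and three ten-day cycles at 7, 8 and 9 months", and StroVac as three vaccinations within 6–12 weeks. Angocin, D-mannose and saline irrigation run for the whole study.

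On allocation, the Abstract states that "the selection of the protocol will be at the clinicians’ discretion". Section 5 adds: "Patients will be stratified to balance our groups according to age, sex, underlying neurological condition and number of infections prior to study inclusion". Section 7 names t- or Mann-Whitney tests for continuous variables and chi-square or Fisher's tests for categorical ones. It limits the final analysis to patients with at least 6 months of follow-up who stayed on one regimen.

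**The concern.** The plan treats earlier antibiotic prophylaxis as a reason for exclusion, and a change of regimen after entry as a reason to leave a patient out of the analysis. It has no rule for a change of regimen just before entry.

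That gap matters most for OM-89 and StroVac. Both schedules leave long stretches of follow-up without dosing, and infections in those stretches still count towards the regimen. A patient who finished StroVac four months ago and enters on D-mannose would, had StroVac been the study regimen, still be inside StroVac's 12-month follow-up. The infections are counted under D-mannose.

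The aim is to compare five regimens and pick candidates for a randomised trial (Sections 1.1 and 2). If the share of patients with residual vaccine effect differs between arms, part of the observed ranking reflects treatment history. The unnumbered antibiotic window is a smaller fault of the same kind, since sites can apply it differently.

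**Working it through.** **1. No plan figure is at issue.** The document gives no number for prior exposure or carry-over, so there is none to reproduce, and the sample size is unaffected.

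**2. How long the plan credits a regimen after dosing (Section 6.2 schedules, 12-month follow-up).**
- OM-89: about 90 days plus 3 × 10 days = 120 dosing days. Days without dosing: 365 − 120 = 245, and 245/365 = 67%.
- StroVac: course completed by week 6 to week 12. Weeks after the course: 52 − 12 = 40 to 52 − 6 = 46, or 77% to 88% of the year.
- Angocin, D-mannose, irrigation: dosed throughout, so their schedules imply no effect beyond dosing.

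These percentages show only that the plan relies on effects outlasting dosing for two regimens. They do not measure the bias.

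**3. Does any stated rule catch a patient who switches before entry?**
- Eligibility (4.1, 4.2): no. Only antibiotic prophylaxis is excluded.
- Infection-count criterion: not reliably. Entry needs more than 3 episodes in 12 months. At the plan's mean of 9.4 per year, a reduction of 3 leaves 9.4 − 3 = 6.4, which still qualifies.
- Balancing (5): no. The number of prior infections is a factor, but the prior regimen is not.
- Analysis set (7): no. The same-regimen rule looks forward from entry.
- Named tests (7): no. They are unadjusted.
- Baseline record (6.1): in part. Prior regimen, duration and dosing are known, but the time since stopping is not.

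**4. Does a patient already on the same regimen qualify?** The item in Section 4.1 can be read as met by such a patient. The Abstract has regimens starting after inclusion, with follow-up from onset, and Section 4 says prophylaxis will be offered. The texts point different ways.

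**5. Illustration of sensitivity only.** Assumptions not in the documents: equal arms of 785/5 = 157; two equally effective regimens; and a carry-over of 3 UTIs per year in each affected patient, borrowing the Section 7 threshold for a clinically significant reduction. The SD of 5.414 is from Section 7.
- SE of a two-arm difference = 5.414 × √(2/157) = 0.61.
- Spurious difference = 3 × (gap between arms in the share of affected patients).
- False-positive rate at nominal two-sided 5% = Φ(b/SE − 1.96) + Φ(−b/SE − 1.96), where b is the spurious difference.

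| Gap in share | b (UTIs/year) | False-positive rate |
|---|---|---|
| 10 points | 0.3 | 8% |
| 20 points | 0.6 | 17% |
| 30 points | 0.9 | 31% |
| 50 points | 1.5 | 69% |

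If only half the effect persists (1.5 per year), gaps of 20 and 40 points give the same 0.3 and 0.6. With no gap or no persistence, b is zero.

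**The case against.** The strongest reply is that this is an observational study of routine prescribing, meant to find candidates for a later trial. Admitting previously treated patients is defensible there. Earlier regimens are already recorded, and the choice of adjustment is often left to an analysis plan, which is not shown. This stands in part: previously treated patients need not be turned away. But the eligibility lists are set out in full in this document, the antibiotic window in them is unnumbered, and an analysis plan cannot recover a stop date that was never collected.

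Three stronger readings are tempting, and the documents do not support them.

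- A reader might infer that patients already failing a regimen are enrolled on that same regimen. The Abstract and Section 4 point to a new start, so this is an ambiguity and not an established flaw.
- A reader might take the off-dosing percentages, or the table above, as the size of the bias. Neither the share of entrants with a recent course nor the persistence of effect is in the documents, and 3 UTIs per year is a threshold of clinical significance, not a vaccine effect. Patients who still have more than 3 infections after a recent course are also less likely to be strong responders, so applying a full carry-over to each leans high.
- A reader might conclude that the primary comparison should be confined to patients with no non-antibiotic prophylaxis for 12 months. The carry-over argument rests on the OM-89 and StroVac schedules alone, and such a restriction could remove many patients from five arms.

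Moving patients who failed one regimen to another is channelling under clinician choice. It is not a washout fault, though adjustment for prior regimen helps with it.

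**Conclusion.** The point holds for patients coming from a different study regimen. The plan as written admits them, does not record when the earlier regimen stopped, does not balance on it, and names only unadjusted tests, while its own schedules presume that OM-89 and StroVac act well beyond dosing. Residual effect can therefore be credited to the wrong arm.

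The size and net direction of any distortion cannot be determined from the documents. Bias in a comparison requires both that some effect persists and that recent OM-89 or StroVac use is unevenly spread across arms. Clinician choice makes the second possible, but nothing shows that it occurs. The position of patients already on the same regimen is unresolved, and Section 4.1 and the Abstract must be reconciled. The unnumbered antibiotic window is a definite gap in wording.

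**What to change.** - Section 4.2: state the number of months in the antibiotic-prophylaxis exclusion.
- Section 4.1 and Abstract: reconcile them on whether entry requires a new start of the regimen.
- Section 6.1: add a stop date to the earlier-prophylaxis item, and classify each patient at Day 0 as no recent regimen, a different regimen, or the same regimen, with the meaning of recent fixed in advance.
- Section 7: keep all otherwise eligible patients in the primary regimen comparison, whatever their prior regimen, but adjust it for prior regimen. Prespecify a sensitivity analysis that excludes patients with a recent course of a different regimen, in particular OM-89 or StroVac within 12 months, which matches the period over which the plan credits a regimen.

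The cost is one extra eCRF field, some analysis wording and lower precision in the sensitivity analysis. No visits are added, and no patient is turned away because of an earlier study regimen. Stop dates are best captured at enrolment, since they are harder to reconstruct later.

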### 4.3. Consent

Data collection in centres in Germany and Switzerland will fall under general consent. If necessary, because of country-specific ethical board requirements, patients will need to give written consent. Consent will be obtained by the primary physician. 

## 5. Patients Recruitment

Identification of observations: Patients to be observed will be identified through participating clinicians in either an outpatient setting, hospitalised patients or follow-up visits after symptomatic infections. The eligibility criteria checklist of all cases considered to be observed will be filled in by participating principal investigators (PI). Clinical information from the initial diagnosis should be used to assess eligibility.

A logbook of patient screening will be kept to keep track of the number of patients per unit who are eligible and who are not. We will also keep track of those who are eligible and refuse to participate. If recruitment rates are slower than the anticipated trajectory, the logbook will be reviewed to identify obstacles in recruitment. 

Patients will be stratified to balance our groups according to age, sex, underlying neurological condition and number of infections prior to study inclusion. 

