We have recourse to a broad armamentarium of non-antibiotic options, whereby significant evidence is limited. Several viable and readily available options have been shown to yield consistent results. Main alternatives to antibiotic prophylaxis include vaccines, antiseptics, urine-specific antimicrobials, and direct mechanic washouts of the bladder. A variety of vaccines have been used in the prevention of rUTIs. Especially OM-89 (Urovaxom^®^) and the bacterial lysate vaccine Strovac^®^ have been diligently tested and proven to lower the rate of UTI [3,4,5,6]. Additionally, a wide variety of phytotherapeutics is currently in use, especially in Eastern medicine, as a cost-effective and low-threshold, whereas ambivalent efficacy has been reported. A combination of Tropaeoli majoris herba (Nasturtium) and Armoraciae rusticanae radix (Horseradish) demonstrated excellent safety and efficacy in the prevention of recurrent UTIs [7,8]. D-Mannose is another beneficial and cheap prophylactic, therapeutic agent in rUTI with very few side effects [9,10]. Bladder irrigation with various agents, e.g., neomycin, acetic acid, or sterile saline, is also widely used in order to lower bacterial load and defer sedimentation [11,12,13]. 

The main aim of our study is to identify the comparative clinical effectiveness of non-antibiotic prophylaxis regimens in the prevention of rUTI infections in patients with neurogenic bladder dysfunction who practise clean intermittent self-catheterization (CISC). The primary outcome is depicted by the number of breakthrough infections. Secondarily adverse events associated with the prophylaxis regimens and the severity of breakthrough infections must be investigated. 

Change in susceptibility pattern via the optional rectal and perineal swab, as well as health-related quality of life over time (HRQoL) outcomes, will be measured in a random subgroup of 60 patients.

The primary objective is to identify the clinical effectiveness of different prophylactic regimens. The secondary objective is to determine the adverse events related to prophylaxis and the severity of breakthrough infections. 

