## 7. Statistical Considerations

Power analysis was performed to determine an adequate sample size. We considered that these patients suffer 9.4 UTIs per year with an SD of 5.414. Furthermore, we assumed that a reduction of 3 UTIs per year is clinically significant. In order to achieve an effect size of 0.1, 785 participants are necessary (power = 0.87; alpha = 0.05). Furthermore, to achieve an effect size of 0.2, 197 participants are necessary, or for an effect size of 0.3, 88 participants are required, respectively. Data measured on a continuous scale will be expressed as mean, standard deviation, range, and median. Counts and percentages of patients in the categories will be used to convey categorical data. When necessary, T- or Mann-Whitney tests will be performed to determine statistical differences in continuous variables, and Chi-square or Fisher’s tests will be used to test for statistical differences in categorical variables.

Patients with a minimum follow-up of 6 months who remained on the same prophylaxis regimen will be eligible for the final statistical analysis. 

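### Regimen is the clinician's choice, so the promised balancing by stratification has no stated mechanism, and the only tests named are unadjusted: the comparison is open to confounding by indication

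*Protocol article*

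**What the plan says.** Section 3 describes the design: "This is a prospective, longitudinal, multi-arm, multi-centre, observational, clinical cohort study". Section 1.1 gives the purpose: "The main aim of our study is to identify the comparative clinical effectiveness of non-antibiotic prophylaxis regimens". The Abstract states how a patient comes to receive one of the five regimens: "the selection of the protocol will be at the clinicians’ discretion".

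Section 5, on recruitment, then promises comparability: "Patients will be stratified to balance our groups according to age, sex, underlying neurological condition and number of infections prior to study inclusion".

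Section 7 names the tests. For continuous variables, "T- or Mann-Whitney tests will be performed to determine statistical differences in continuous variables"; for categorical variables, "Chi-square or Fisher’s tests will be used to test for statistical differences in categorical variables". Both are to be used when necessary. The article mentions no regression, weighting, matching or stratified test.

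Section 6.1 lists the baseline data to be collected. They include "Number of UTIs in last 12 months", country, Charlson index, catheterisations per day, and earlier prophylaxis with its result.

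**The concern.** Stratification balances treatment groups when someone controls allocation within the strata, or when recruitment is steered by quotas or matching. Where clinicians choose freely, the strata describe the patients but do not decide who receives what. A reader of Section 5 could therefore believe that the five groups will be comparable on the main prognostic factors when nothing in the design makes them so.

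The analysis does not make up for this. A clinician may well choose a regimen in the light of infection history, comorbidity or what has already failed, and these can also predict the number of later infections. An unadjusted two-group test attributes any such difference to the regimen. At stake is the main question of the study, and with it the choice of regimens to carry into the later randomised trial that Section 2 names as the long-term goal.

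**Working it through.** **Step 1. The passages side by side.**

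- Assignment (Abstract): clinician's choice.
- Balance (Section 5): promised on four factors, with no mechanism stated there or elsewhere.
- Comparison (Section 7): four unadjusted tests, none using the four factors.
- Data (Section 6.1): all four factors are collected, with further likely confounders, but no section brings them into the comparison.

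The first two items do not fit together if balance is meant to come from allocation. The last two show that adjustment is feasible but not stated.

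**Step 2. How much a baseline imbalance could matter (illustration only).** The article gives no imbalance or bias figure, so there is none to reproduce. The inputs from Section 7 are a mean of 9.4 UTIs per year, an SD of 5.414, and a clinically significant difference of 3 per year.

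Assume that each patient has a stable rate and that yearly counts vary around it as Poisson. Then:

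- total variance = 5.414² = 29.3
- within-patient variance = mean = 9.4
- between-patient variance = 29.3 − 9.4 = 19.9
- year-to-year correlation = 19.9 / 29.3 = 0.68

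If regimen choice follows the observed prior-year count, and regimens do not differ in effect, the expected spurious difference is correlation × imbalance:

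| Assumed correlation | 1-UTI imbalance | 2-UTI imbalance | 2-UTI result as share of 3 |
|---|---|---|---|
| 0.4 | 0.4 | 0.8 | 27% |
| 0.68 | 0.68 | 1.36 | 45% |
| 0.8 | 0.8 | 1.6 | 53% |

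**Step 3. Effect on an unadjusted test.** Assume an equal split, 785 / 5 = 157 per arm, no true difference, SD 5.414 and a two-sided 5% test between two arms.

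- SE = 5.414 × √(2/157) = 0.61
- chance of a significant result = Φ(b/SE − 1.96) + Φ(−b/SE − 1.96), where b is the spurious difference

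For b = 0.68 this is about 0.20, and for b = 1.36 about 0.60, against a nominal 0.05.

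**Step 4. Sample size does not help.** With 314 per arm, SE = 5.414 × √(2/314) = 0.43. For b = 0.68 the chance of a false positive is then about 0.35. The bias is unchanged, and the larger trial detects it more often.

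**The case against.** The strongest reply is that this is a condensed article and the analysis plan is not shown. Section 7 lists generic tests and does not say that they are the whole primary analysis, and models and covariate sets are commonly left to the analysis plan. That stands as far as it goes: the absence of a model would not be a finding by itself. The point rests on what the article does state, namely a balancing promise that clinician choice cannot deliver and a list of tests that use no baseline factor.

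Secondly, stratification may have been meant as stratified analysis, a recognised way to control confounding in a cohort. This is possible. The sentence sits under recruitment and speaks of balancing groups, which points the other way, and Section 7 does not use the strata. The ambiguity is still a reason to reword the sentence and not simply strike it out, since it holds the only set of confounders that the article names for balancing.

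Thirdly, the figures above are fragile:

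- Section 7 does not say how the SD was obtained.
- The entry criterion of more than 3 infections per year truncates the prior-year count, so the 0.68 need not apply to the enrolled sample.
- If all regimens lowered rates by a common proportion, the carried difference would shrink with it.
- In the other direction, if the groups differed in underlying rate, the imbalance would carry over about one for one. Adjusting for the noisy prior count would then leave about 1 − 0.68 = 0.32 of it.
- The imbalances of 1 and 2 UTIs are assumed.

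Two stronger readings are tempting. A reader might infer that the results will be confounded and that the study cannot answer its question. The documents show only that confounding is possible and not guarded against; they do not say what drives clinicians' choices. A reader might also infer from the footnote to Section 6.2 that product availability differs between countries. That footnote is conditional, concerns the authorisation of vaccines only, and provides for additional arms to be analysed as a subgroup.

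**Conclusion.** The point holds in this form: under clinician choice the balancing promise has no stated mechanism, and the comparison as written is open to confounding by indication. This follows from the text and needs no numerical assumption.

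Its size cannot be known from the documents. On the assumptions in the working, about 0.7 UTI/year per 1-UTI imbalance in prior-year count is a reasonable order of magnitude, with 0.4 to 0.8 as the range over the assumed correlations. That is enough to matter beside a 3-UTI target if the groups differ by 2 or more prior infections.

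The study's openly observational character and its aim of finding candidates for a randomised trial lower the stakes. They do not make an unadjusted ranking of regimens reliable.

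**What to change.** **Section 5.** Replace the balance claim with a statement that regimen is not allocated by the study and that the four factors will be used as adjustment or stratification factors in the analysis.

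**Section 7.** Make the primary between-regimen comparison covariate-adjusted, by regression, with propensity-score weighting as an optional supporting analysis. Include at least prior-year UTI count, age, sex and underlying neurological disease. Add other variables from Section 6.1, such as country, Charlson index, catheterisations per day and earlier prophylaxis. Report baseline balance by regimen, keep the unadjusted tests as descriptive, and state that residual confounding remains, both from unmeasured factors and because a single year's count measures a patient's underlying rate imperfectly.

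**Cost.** Rewording in two sections and modest analysis work. No new data are needed.
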